### The in-home respite intervention

The in-home respite intervention group will receive in-home respite care also called “Baluchonnage” from Baluchon Alzheimer Belgium. Baluchon is a non-profit organization, founded in Québec by gerontologist [name]. She responded to the unmet need of many caregivers willing to take a break from caregiving duties, but lacking a solution for the person with dementia allowing them to stay home in their trusted environment. Eventually from this thought of mind, “Baluchonnage” was originated making it possible for those caregivers to take a short break while a trained support person (also called a “baluchonneuse” or “baluchonneur”) takes in their place. During this break, which can last up to two weeks, the caregiver has time to rest and return with new energy. For the person with dementia other resource use, structure, habits, and all daily activities remain the same. In this way Baluchon not only addresses to caregiver needs, but also to the need of the people with dementia feeling best in their trusted environment [7].

Twenty-four hours before the start of the respite period the “baluchonneur (se)” arrives at the home of the care-recipient. This transition period allows the “baluchonneur (se)” to get to know the environment, get to know the person with dementia and the caregiver, to build a trusting relationship, and to observe daily habits [7].

Additionally to the provision of respite, “Baluchonnage” also includes caregiver support by keeping a support diary during the respite period. In that diary the “baluchonneur (se)” writes down all daily experiences and strategies on how to manage the difficult behaviors the caregivers listed before. This support enables the caregiver to validate theirs perceptions, to learn how to deal with difficult behaviors and to feel understood by somebody. Even after the end of the respite period the “baluchonneur (se)” remains available for further counsel [7]. In Belgium this particular type of respite is not subsidized by the National Health Care Insurance.

Finally, based on ethical considerations, we cannot prohibit intervention participants from having multiple Baluchonnage-periods or utilize other standard dementia care services or supportive services including respite care. Especially not since some supportive respite care services such as: day care, night-time care (in-home or in a residential setting), and temporary residential admission are considered standard care in Belgium. Because use of other services or having multiple in-home respite periods via Baluchon can potentially influence study results, the extent of use will be captured with the RUD questionnaire (Resource Use in Dementia) [18].

### The control group - non in-home respite care

The control group receives usual dementia care. This means that they can have all types of standard dementia care (including medical, psychological, and other health and social services) and other supportive initiatives for informal caregivers including other types of respite care. As mentioned before, control group dyads who already utilized in-home respite from Baluchon, which is not considered standard dementia care in Belgium, will not be allowed for inclusion. Another reason for exclusion at baseline is not being eligible or willing to consider in-home respite via Baluchon.

### Sample size

Sample size calculation was performed using SPSS SamplePower 3®. First, literature was searched to determine the needed effect size and standard deviation (SD) allowing to distinguish a statistical significant and clinical relevant difference in the primary outcome, i.e. burden. Based on the findings of a similar high quality intervention study an effect size of 0.4 was used in the analysis, which implies a difference of six points on the ZBI scale (Zarit Burden Interview), and a SD (standard deviation) of 15 [19]. Also, an average drop-out rate of 20% was taken into account, a power of 80% and a significance level at 0.05. Based on these values a total of 124 caregiver/care-recipient dyads will be needed for the intervention group.

To reduce selection-bias inherent to quasi-experimental studies an allocation ratio of 1:2 will be used to allow matching techniques. As a result 248 caregiver/care-recipient dyads will be needed in the control group.

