### Statistical analysis

First of all, descriptive statistics will be represented to draw a clear profile of the characteristics of study participants. Therefore the mean, percentages, and the standard deviations of quantitative variables will be displayed. To determine possible baseline differences between the groups, mean values of baseline characteristics will be compared using independent sample t-tests for continuous variables if normally distributed or by performing Pearson’s chi-square test for categorical variables. To help control for bias and confounding, statistical techniques such as propensity score matching will be used. Propensity score matching can be seen as a tool to simulate a RCT setting. In this way we can expect the observed effect to be an unbiased estimate of the real effect [41, 42].

To investigate possible effects of the intervention on the primary and secondary outcomes, analysis of variance will be conducted if the outcome variables are normally distributed. A *P*-value of 0.05 will be considered as significant. All analyses will be based on intention to treat also taking drop-outs into account and avoiding overestimation of respite care effects.

When the intervention is effective a cost-effectiveness analysis in a separate economic evaluation plan will be performed. ICERs will be calculated for the mean and upper and lower confidence levels of the costs and consequences. To explore uncertainty one-way-sensitivity analysis will be conducted around the ICER and illustrated in a Tornado diagram. Additionally, on all input variables a probabilistic sensitivity analysis, also called Monte Carlo analysis, will be conducted to test robustness of the model. These results will also be illustrated. Finally, the results and the willingness to pay threshold of the Belgian Health Care System will be presented in a cost-effectiveness acceptability curve [34].

To compare time to nursing home placement of persons who use respite care to those who do not, we will use Kaplan-Meier survival curves to illustrate association between the comparison groups. By additionally conducting a log-rank test statistical difference between the groups in time to placement can be found [43].

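### The 80% power belongs to an unmatched 1:1 comparison; with 1:1 matching it is a best case, because nothing is held in reserve for intervention dyads that find no match

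*Protocol article*

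**What the plan says.** All the inputs stand in the protocol article under Sample size: "an effect size of 0.4 was used in the analysis, which implies a difference of six points on the ZBI scale", "and a SD (standard deviation) of 15", "an average drop-out rate of 20% was taken into account", and "a power of 80% and a significance level at 0.05". The section concludes: "Based on these values a total of 124 caregiver/care-recipient dyads will be needed for the intervention group".

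The next paragraph of the same section turns to selection bias and says that "an allocation ratio of 1:2 will be used to allow matching techniques". From this follow 248 control dyads, twice 124.

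Under Statistical analysis, "statistical techniques such as propensity score matching will be used" to deal with bias and confounding, and outcomes are to be compared by analysis of variance if normally distributed. No covariate is named for that analysis. The same section adds: "All analyses will be based on intention to treat also taking drop-outs into account". The article gives no matching ratio, no expected match rate and no power for a matched comparison.

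**The concern.** The power statement and the matching plan sit in consecutive paragraphs but are not connected. The intervention number was fixed first, and the ratio was added for another purpose. Doubling the controls protects against discarding controls. It does not protect against losing intervention dyads that have no acceptable control, and 124 has no slack for that.

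The article itself makes such losses foreseeable:

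- **Recruitment:** intervention dyads are people who approach Baluchon for respite. Controls come from general practitioners, memory clinics, expert centres and a sickness fund.
- **Study participants:** earlier Baluchon use is allowed in the intervention group and excluded in the control group, so no control can be matched on it. The Discussion expects previous users to react differently.
- **Discussion:** lower socioeconomic and educational groups are expected to be under-represented in the intervention group, and propensity matching is offered as the response.

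At stake is whether 80% can be read as the power of the comparison the trial will report, and to which dyads that comparison applies.

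**Working it through.** **Inputs (Sample size section).** Difference 6 ZBI points, SD 15, so d = 6/15 = 0.4. Power 80%, alpha 0.05, drop-out 20%. Sidedness is not stated. I take two-sided, because one-sided gives 78 per group and 98 after drop-out, not 124.

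**Step 1: reproduce 124.** For two equal groups, n = 2(1.960 + 0.842)² / 0.4² = 98.1, rounded up to 99 per group. Allowing for drop-out, 99 / 0.8 = 123.75, rounded up to 124. This matches the article.

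**Step 2: did the 1:2 ratio enter?** With two controls per intervention dyad, the intervention number is 1.5(1.960 + 0.842)² / 0.4² = 73.6, so 74, with 148 controls. After drop-out: 74 / 0.8 = 92.5, so 93, and 148 / 0.8 = 185. These are not 124 and 248, so the ratio was applied afterwards.

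**Step 3: power after matching.** I start from the 99 expected intervention completers. Power comes from the two-sample t test with noncentrality 0.4 × √(n₁n₂/(n₁+n₂)), with no within-pair correlation and no covariate adjustment. The unmatched share is an assumed range.

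| Intervention completers unmatched | Matched | Noncentrality 1:1 | Power 1:1 | Noncentrality 1:2 | Power 1:2 |
|---|---|---|---|---|---|
| 0% | 99 | 2.81 | 80.0% | 3.25 | 90.0% |
| 10% | 89 | 2.67 | 75.6% | 3.08 | 86.6% |
| 20% | 79 | 2.51 | 70.5% | 2.90 | 82.4% |
| 25% | 74 | 2.43 | 67.6% | 2.81 | 79.9% |
| 30% | 69 | 2.35 | 64.5% | 2.71 | 77.0% |

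The 1:2 columns assume that every matched intervention completer has two completing controls. Break-even for 80% under 1:2 is 74.2 matched intervention completers, and 1 − 74.2/99 = 25%.

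**Step 4: what baseline adjustment recovers.** If baseline and six-month ZBI correlate at r, the residual SD is 15√(1 − r²). At r = 0.5 it is 15 × √0.75 = 12.99, so d becomes 6/12.99 = 0.462. With 79 per group, power is 82%, against 70% unadjusted. At r = 0.3 it is about 75%. The article gives no correlation, so both values are assumptions.

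**The case against.** The strongest reply is that the article makes no arithmetic error. Its 124 follows from its inputs, and 80% does describe a real case: complete 1:1 matching, 99 against 99. The doubled control pool is itself an allowance for matching, and half the controls can be discarded under 1:1 without touching the planned power. Ratio, caliper and the handling of unmatched dyads may properly be left to an analysis plan that is not shown. The match rate is unknown, and within-pair correlation or baseline adjustment could win back what is lost. All of this stands, and it limits the point to the meaning of the 80% and the missing reserve on the intervention side.

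A reader might go further in four ways that the article does not support.

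- **That 80% fits no form of matching.** It fits complete 1:1 matching exactly.
- **That 1:2 matching uses every control and so cannot reduce bias.** This holds only if each intervention dyad must take two controls however distant. With a caliper, selection takes place. In simulated 1:2 matching with assumed propensity-logit separations of 0.5 to 1.2 SD, roughly 135 to 196 of the 248 controls were used.
- **That the trial's power is some figure in the 60s or 70s.** Any single figure rests on an assumed match rate. The table is a range and not an estimate.
- **That matching contradicts the intention-to-treat statement.** That needs a rule to discard unmatched dyads, which the article never states. Its wording names matching as one technique among others and ties intention to treat to drop-outs.

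**Conclusion.** The point holds in a limited form. The 80% is correctly calculated, but for an unmatched 1:1 comparison of all 99 intervention completers per group. As a statement about the matched design it is a ceiling under 1:1 matching without adjustment, falling by about 4, 10 and 15 percentage points at 10%, 20% and 30% unmatched. Under 1:2 matching it is conservative until about 25% are unmatched. The direction therefore depends on a ratio that the article does not fix.

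The result rests on d = 0.4, two-sided 5%, exactly 20% drop-out, no within-pair correlation, no covariate adjustment and an assumed unmatched share. The recruitment plan makes some loss of intervention dyads likely, but the article does not allow its size to be estimated. The sponsor should clarify the power statement; the sample size need not change.

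**What to change.** Keep 124 and 248.

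1. **Sample size:** say that the 80% assumes every intervention completer is matched 1:1. Name the matching ratio to be used and give power over a range of match rates, for example the relevant column of the table above.
2. **Statistical analysis:** for the primary outcome, replace the analysis of variance with no stated covariate by a comparison of six-month ZBI adjusted for baseline ZBI. The baseline value is already collected in both groups (Tables 1 and 2). State the correlation assumed if power is quoted for it.
3. **Reporting:** give the number of intervention dyads left unmatched, and describe the matched estimate as applying to the matched dyads.

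Full matching or propensity weighting, which would keep nearly all dyads, is an option and not a necessary correction. If chosen, power should be stated from the effective sample size.

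The cost is a few sentences and a recalculated table, with no extra dyads or assessments. The drawback is a power statement that is conditional and, under 1:1 matching, possibly below 80%.

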### Recruitment

Participants of the intervention group will be recruited by Baluchon staff when asking for a first or a new period of in-home respite care. First, Baluchon staff will describe the study to the dyads and ask them about their preparedness to participate. When they give their verbal consent, contact information will be forwarded to the research team who will then contact them by phone. During this call a home visit will be planned to sign the informed consent and complete the baseline assessment. In return for their participation, participants will receive the respite care for free during five days.

Participants for the control group will be recruited by several general practitioners spread over the different regions in Belgium, by physicians affiliated to the participating Belgian memory clinics, by several Belgian expert centers dementia, and by a Belgian sickness fund. Similar to the recruitment of the intervention group, the physician will give some information about the study. When verbal consent to participate is given to the physician, caregivers will be contacted by phone by the research team to check eligibility. This will be done by listing different support strategies (including “Baluchonnage”) and ask the caregiver if they would be interested to receive this type of support. When caregivers appear to be eligible the research team will plan a home visit to sign the informed consent and complete the baseline assessment.

### Data collection

Data collection of caregiver and care-recipient characteristics and research outcomes will be conducted at several assessment moments (Fig. 1). The baseline assessment will be conducted during a home visit by a member of the research team. Background characteristics and baseline values of the research outcomes will be gathered during this assessment. For the intervention group this will be in the week preceding the respite period. For the control group this will take place after inclusion. Two weeks after having the respite period possible changes in some of the study outcomes will be measured in the intervention group. Six months after inclusion, at the primary endpoint of this trial, all research outcomes (except time to nursing home placement) as well as some background characteristics (i.e. activities of daily living, dementia severity, dementia specific medication use & time spent in caregiving) will be measured again. Finally, 12 months after the baseline assessment, at secondary endpoint, some of the research outcomes will be measured again as well as time to nursing home placement.

**Fig. 1 Fig1:**
[figure not shown]
timeline of primary and secondary endpoints of the trial

To fulfill the assessments after the baseline assessment, caregivers will be contacted by telephone. This interviewing technique was chosen because it is the closest approach to face-to-face-interviewing which is not achievable in this trial due to time constraints and practical and organizational limitations. Permission to use the scales were asked to the authors or to the organizations responsible for the distribution of a certain questionnaire. All questionnaires are available in Dutch and French for use in Belgium. When no valid translation of a certain questionnaire existed in Dutch or French for Belgium a forward-back translation method was performed. In this method three phases were completed. First, a forward translation was done. This step was followed by a backward translation by another independent translator who had no knowledge or had no contact with the original questionnaire. During a last reconciliation phase, the original questionnaire was compared with the backward translation. In this way, discrepancies of translation were identified and corrected.

### Research outcomes and instruments

The trial will evaluate outcomes in the caregiver as well as in the care recipient (measured via the caregiver) and the healthcare system (Tables 1 and 2). The primary research outcome is caregiver burden. Secondary outcomes for caregivers are: health related quality of life and reactions to behavioral problems of the care-recipient. A secondary outcome related to the care-recipient is: frequency of behavioral problems. Secondary outcomes related to the healthcare system are: intention to institutionalize the recipient into a nursing home, and resource use of the recipient. Finally, in a follow up phase of the trial possible differences in time to nursing home placement will be measured (as well as burden and intention to institutionalize). Additionally, willingness to pay for “Baluchonnage” per day will be asked to the informal caregivers (Fig. 1, Tables 1 and 2).

**Table 1 Tab1:** Data collection of the intervention group at the different assessment moments

Intervention group	Baseline (T0)	14 days after intervention (T1)	T0 + 6 months (T2)	T0 + 12 months (T3)
Background characteristics				
Age CG + CR	X			
Gender CG + CR	X			
Region CG + CR	X			
Etnicity CG + CR	X			
Marital status CG + CR	X			
Educational level CG + CR	X			
National Registration Number CR	X			
Relationship with CR	X			
Living situation of CG	X			
Employment status CG	X			
Waiting list nursing home	X			
Medication use Dementia-specific CR	X		X	
Earlier use of Baluchon	X			
Reason for respite	X			
Time spent in caregiving	X		X	
Severity of dementia CR	X		X	
ADL functioning CR	X		X	
Research outcomes				
Quality of life of CG	X		X	
Burden of CG	X	X	X	X
Frequency of behavioral problems of CR	X	X	X	
Reaction of CG on behavioral problems of CR	X	X	X	
Intention to institutionalize the CR	X	X	X	X
Resource use CR	X		X	
Willingness to pay			X	
Time to nursing home placement CR				X

*CG* Caregiver, *CR* care-recipient, *ADL* Activities of Daily Living

**Table 2 Tab2:** Data collection of the control group at the different assessment moments

Control group	Baseline (T0)	14 days after intervention (T1)	T0 + 6 months (T2)	T0 + 12 months (T3)
Background characteristics				
Age CG + CR	X			
Gender CG + CR	X			
Region CG + CR	X			
Etnicity CG + CR	X			
Marital status CG + CR	X			
Educational level CG + CR	X			
National Registration Number CR	X			
Relationship with CR	X			
Living situation of CG	X			
Employment status CG	X			
Waiting list nursing home CR	X			
Medication use dementia-specific CR	X		X	
Earlier use of Baluchon	X			
Preparedness to receive in-home respite	X			
Reason for respite			X	
Time spent in caregiving	X		X	
Severity of dementia CR	X		X	
ADL functioning CR	X		X	
Research outcomes				
Quality of life of CG	X		X	
Burden of CG	X		X	X
Frequency of behavioral problems of CR	X		X	
Reaction of CG on behavioral problems of CR	X		X	
Intention to institutionalize the CR	X		X	X
Resource use CR	X		X	
Willingness to pay			X	
Time to nursing home placement CR				X

*CG* Caregiver, *CR* care-recipient, *ADL* Activities of Daily Living

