An additional review, that also allowed observational designs without control group, was conducted to investigate the effectiveness of different types of respite care. In this review it was concluded that day care services are effective in decreasing caregiver burden and behavioral problems in people with dementia, but also accelerate time to nursing home placement. Results of temporary residential admission were rather mixed and showed unexpected adverse effects on both caregivers and care-recipients. No comparable evidence was found for night-time care in residential settings. Evidence on community-based respite care, including in-home respite care and host family respite care, is rare as well. Only one in-home respite care intervention was identified indicating some benefits for caregivers. Finally, there was no research on cost-effectiveness of any of the investigated types of respite care. As a result, the authors concluded that there is a need for new intervention studies measuring effectiveness and investigating cost-effectiveness of respite care. Especially the effect of an in-home respite program on the caregiver, the care-recipient, and the healthcare system should be further investigated [14].

On the other hand, substantial qualitative research indicated high satisfaction and positive perceptions regarding respite care in general and pointed out that breaks are crucial if caregivers are to continue to keep their loved ones home. Additionally, many caregivers pointed out their preference for in-home respite care, especially because in this way their loved ones can stay in their trusted environment [14].

Because current evidence suggests that respite services can actually be important and effective strategies for caregivers, but that the level of evidence should be further established in terms of effectiveness, especially for in-home respite care, we designed a quasi-experimental study to assess the effectiveness of an in-home respite care program compared to a control group not receiving the same type of in-home respite on the well-being of the caregiver, the care-recipient, and on the healthcare system. The latter in terms of resource use, intention to institutionalize the care-recipient, and time to nursing home placement.

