#### Time to nursing home placement

Finally, the time to nursing home placement will be obtained by measuring the interval from the date of study enrollment to the date of permanent nursing home placement. Short term admissions in nursing home placements do not count as definitive nursing home placement. It is expected that even at 12 months a majority of patients will not be institutionalized. Hence, this parameter is to be considered as a secondary endpoint.

Additionally, the National Registration number of care-recipients will be obtained to allow us to trace study participants in the IMA database (Intermutualistisch Agentschap) and gather information on their date of placement in a nursing home over a longer time period than the trial.

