### Background characteristics

For caregivers we will obtain the following background characteristics: age, gender, region, marital status, ethnicity, educational level, relationship with the care-recipient, employment status, living situation, and time spent in caregiving. In both study groups the reason for (potential) use of respite will be asked based on evidence from the study of Connell et al. (2012) [30]. Earlier use of Baluchonnage will also be questioned to intervention group participants (Tables 1 and 2).

For the care-recipient the following background characteristics will be collected: age, gender, marital status, ethnicity, region, National Registration Number, educational level, being on a waiting list for long-term nursing home placement, dementia-specific medication use, activities of daily living (Belgian Katz scale), and severity of dementia (GDS). In a later phase, the National Registration Number of the person with dementia will allow us to trace study participants in the IMA database (Intermutualistisch Agentschap) and gather information on resource use and date of placement in a nursing home over a longer time period than the trial (Tables 1 and 2).

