Another important limitation of this trial is a consequence of not controlling the exact duration of the received in-home respite care period in the intervention group. The latter would not be acceptable due to ethical considerations and limited capacity of Baluchon Alzheimer Belgium. Even by setting a minimum duration of five days as an inclusion criterion, differences in outcome variables can still be caused by differences in duration. Nevertheless, to minimalize this phenomenon subgroup analyses can be undertaken. The same applies for intervention dyads who already received in-home respite in the past. After all, we can expect that dyads who are already familiar with in-home respite care react differently from people who are about to utilize it the first time. It is known that trust plays a crucial role in accepting respite care [44, 45]. Finally, use of other supportive strategies such as day care or night-time care can also influence results for which subgroup analyses can be undertaken if necessary.

Like other supportive interventions for caregivers this study only has a rather limited duration and a short follow up period. A longer time period could produce different outcomes or show certain effects to be strengthened, weakened, or sustained over time. Because dementia is a slow degenerative process, it can be expected that differences in time to nursing home placement between the study groups will not be found on such short notice. Therefore, to allow conclusions about possible difference in time to placement, we will measure intention to institutionalize which is seen as an adequate predictor for real placement into a nursing home [46]. Also, we will obtain the National Registration Number of dementia participants allowing to trace information on resource use and time to nursing home placement over a longer time period than the trial. Finally, we will perform modeled-based cost-effectiveness analyses to extrapolate results over a longer period.

Due to time constraints, organizational limitations, and high geographical distribution of study participants, assessments after the first baseline assessment will be done by telephone interviewing. Although no evidence was found indicating that the used instruments are not suited for telephone interviewing and data collection by telephone is widely performed and well accepted, face-to-face interviewing still remains the most preferred type of collecting data.

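### Nursing-home waiting-list status is asked at T0 only, so registrations during the trial go unrecorded, and the placement comparison as described does not separate dyads already listed at entry

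*Protocol article*

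**What the plan says.** Table 1 (intervention) has the row "Waiting list nursing home" and Table 2 (control) the row "Waiting list nursing home CR". Each is marked in the T0 column only. The Background characteristics section lists "being on a waiting list for long-term nursing home placement" among the care-recipient items. The Data collection section names the background items measured again at six months as "activities of daily living, dementia severity, dementia specific medication use & time spent in caregiving"; waiting-list status is not one of them.

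The placement outcome is obtained by "measuring the interval from the date of study enrollment to the date of permanent nursing home placement", and short stays do not count. The Statistical analysis section compares the groups with Kaplan-Meier curves and a log-rank test and mentions no stratification. Propensity score matching is planned, without a covariate list.

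The article is open about the limits of this outcome: "It is expected that even at 12 months a majority of patients will not be institutionalized", and in the Discussion, "it can be expected that differences in time to nursing home placement between the study groups will not be found on such short notice". For that reason it also measures intention to institutionalize, at T0, T2 and T3 in both groups and at T1 in the intervention group. It also plans linkage to the IMA database for placement dates after the trial.

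**The concern.** The plan recognises that placement can run through a waiting list, yet observes the list only once. Two things follow.

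First, a dyad that registers after T0 and is still waiting at month 12 looks the same in the placement data as one that never sought a place. Registration lies between wishing for placement and moving, and nothing shown records or dates it.

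Second, a dyad already listed at T0 is not excluded. If its bed comes up it is an event, although the decision came before the study. Intervention dyads enter when they ask for respite; controls come through general practitioners, memory clinics, expert centres and a sickness fund. The share already listed could differ between them in either direction.

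This matters because research question 3 names time to admission, and because the article's own review of day care found that such services reduce burden "but also accelerate time to nursing home placement". Hastened placement is therefore an effect the trial should be placed to notice.

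**Working it through.** **1. The schedule, item by item**

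| Item | T0 | T2 | T3 |
|---|---|---|---|
| Waiting-list status, both groups | yes | no | no |
| Intention to institutionalize, both groups | yes | yes | yes |
| Time to permanent placement, both groups | – | – | yes |

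The resource-use questionnaire, given at T0 and T2, is described as covering services used and caregiving time. Registration is not mentioned.

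**2. What each kind of dyad contributes to the 12-month comparison**

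- Not listed at T0, registers, still waiting at T3: no event.
- Not listed at T0, never registers: no event, so not distinguishable from the dyad above.
- Listed at T0, bed arrives by T3: an event, from a decision made before the study.

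**3. Confounding by T0 status**

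Let p be the share listed at T0 in a group, a the 12-month placement risk if listed, and b the risk if not. With no intervention effect, the crude difference in placement between groups is (p_intervention − p_control) × (a − b). It is zero only if the groups are balanced on list status or if listing does not predict placement. The documents give none of these quantities, so no size can be attached.

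**4. The plan's own figure**

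The only sample size stated is for burden. With a difference of 6 points and SD 15 (effect 0.4), two-sided 0.05 (sidedness assumed) and 80% power:

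n = 2 × (1.96 + 0.84)² / 0.4² = 98, rounded up to 99 per group; 99 / 0.8 = 123.75, i.e. 124. Controls: 2 × 124 = 248.

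The stated 124 and 248 are reproduced and are not affected by this point. No event count or power is given for placement.

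**5. What recording registration could add**

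Assumptions, none from the documents: 298 dyads followed (372 × 0.8), allocation 1:2, two-sided 0.05, and the same hazard ratio (HR) for registration as for placement. Formulae:

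- Power = Φ(√(events × 1/3 × 2/3) × |ln HR| − 1.96)
- Events needed for 80% power = (1.96 + 0.84)² / (2/9 × (ln HR)²): 136 at HR 0.6 and 215 at HR 1.5

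Placement alone, at assumed 12-month rates of 5% to 30% (15 to 89 events), has power of 15% to 62% at HR 0.6 and 11% to 44% at HR 1.5.

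| Event rate: placement only → with registration | Power, HR 0.6 | Power, HR 1.5 |
|---|---|---|
| 10% → 15% | 26% → 36% | 18% → 25% |
| 15% → 20% | 36% → 46% | 25% → 31% |
| 15% → 25% | 36% → 55% | 25% → 38% |
| 20% → 30% | 46% → 62% | 31% → 44% |

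Worked case, 15% at HR 1.5: 298 × 0.15 = 44.7 events; √(44.7 × 2/9) = 3.15; 3.15 × 0.405 = 1.28; 1.28 − 1.96 = −0.68; power 25%.

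HR 1.5 is the column for hastened placement. The table is generous: a supportive analysis restricted to dyads not listed at T0 would have fewer than 298, and matching may remove more.

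**The case against.** The strongest reply is that the plan has already dealt with early placement. It says that differences are unlikely within a year, makes placement secondary, repeats the intention scale in both groups as a predictor of placement, and links to a database for later admissions. The permanent move is a coherent event for a question about admission. Registration is a different and softer outcome, since families may list as a precaution. T0 list status is collected in both groups and so is available for the propensity score, and the choice of covariates is commonly left to a fuller plan.

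Most of this stands, and it rules out several stronger readings that a reader might infer:

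- *The trial cannot see hastened placement decisions.* Not supported. The intention scale is repeated for this purpose. The article describes it as measuring desire and does not show the wording of its six items, so whether any item captures a concrete step cannot be judged.
- *Research question 3 is left without an answer.* Not supported. It also covers resource use and intention, and linkage can find the later admission of a dyad still waiting at month 12.
- *The missing item causes the low event count.* Not supported. The 12-month horizon and the sample size are the main causes.
- *Bed waits remove a calculable share of events.* Not supported. Dyads listed before T0 are placed during the year and offset those still waiting at its end, so the net change cannot be derived from the documents.

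What the reply does not meet is narrower. The intention scale is not shown to date an application. Linkage is described for placement dates and resource use, not registration. The limitation disclosed is the short horizon, not the waiting list. The T0-only schedule is stated in the tables, not left open.

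**Conclusion.** The point holds as a small, inexpensive improvement. Two facts carry it: list status is scheduled at T0 only, and the placement comparison as described mixes dyads whose decision predates the study with those whose decision does not, in groups that were not randomised. The resulting bias could run either way and cannot be sized from the documents; the T0 data will show how unequal the groups are.

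The gain from recording registration is moderate and rests on assumed rates: about 6 to 13 percentage points of power at HR 1.5 and 10 to 18 at HR 0.6 (differences within the table rows). It does not bring the 12-month comparison to 80% power in any case examined. Its main value is a dated action between desire and admission. The primary outcome is untouched.

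**What to change.** 1. State that the time-to-placement comparison will be stratified by, or adjusted for, waiting-list status at T0. The variable is already collected, so this costs nothing in data collection.
2. Repeat the waiting-list item, with month of registration, in the T2 and T3 telephone calls in both groups. This is one question in two calls already planned.
3. Among dyads not listed at T0, report time to first registration or permanent placement as a supportive secondary outcome beside placement, not in its place. This is one extra analysis.

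The drawback is that precautionary registration makes the added outcome softer than placement. It should be labelled supportive and read together with the intention scale and the linked admission dates.
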